### Specific Aim 2– To evaluate the kinematic and kinetic differences of non-articulating ESR, articulating ESR, and active plantar flexion ESR feet in individuals with transtibial amputation

Hypothesis 2.1 Plantarflexion forces (i.e. ground reaction forces) at push off /terminal stance will be most symmetrical to the intact limb for active plantarflexion devices, followed by non-articulating ESR feet, and lastly articulating ESR devices.

Hypothesis 2.2 Biomechanical symmetry in gait while negotiating a decline will be greater for both active plantarflexion ESR and articulating ankle ESR conditions compared to non-articulating ESR feet.

Hypothesis 2.3 Biomechanical symmetry in gait while negotiating an incline will be greatest for devices with active plantarflexion, followed by articulating devices, and lastly non-articulating ESR feet.

Hypothesis 2.4 Ambulation at a faster than self-selected walking speed will yield decreased symmetry in articulating ankle ESR and non-articulating ESR feet but not with the active plantar flexion ESR feet.

Hypothesis 2.5 Articulating ESR feet will not yield significant differences in gait symmetry regardless of specific foot assigned within the articulating ESR category.

**Specific Aim 3 – To correlate biomechanical findings with functional and subjective outcome measures and with user preference determined through activity monitoring and user satisfaction to develop guidelines for appropriate prosthetic prescription.**

Hypothesis 3.1 Individuals that commonly negotiate ramps, hills, inclines or declines will show preference for an articulating ankle ESR and/or active plantarflexion ESR feet over non-articulating ESR feet

Hypothesis 3.2 Individuals that have higher step counts, but do so at a low activity level will prefer the active plantarflexion ESR ankle-foot prosthesis.

Hypothesis 3.3 The majority of subjects will chose to utilize a single prosthesis for all activities, and not use different prostheses for different activities, as measured through step activity monitoring and daily activity logs.

Hypothesis 3.4 Step activity performance will, and age will not, correlate with prosthetic feet category that best optimizes function.

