## **Specific Aim 2:**

Specific Aim 2 will be addressed through a subset of  $n=30$  subjects which will undergo kinematic and kinetic biomechanical evaluations at the completion of each acclimation period for Parts 2-4. This will include kinetic and kinematic evaluation on level ground walking, and additional kinematic evaluation on inclines and declines.

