### **SA2 Statistical Analysis:**

To address the hypotheses stated for SA2, several parameters, including temporal-spatial variables (step lengths, stance/swing times, cadence, and stride length), peak angles, moments, and powers for the ankles, knees, and hips during each phase of gait, and other biomechanical parameters (external adduction moment rate, impulse external knee adduction moment, peak vertical ground reaction force, peak resultant ground reaction force, etc.) will be measured and statistically compared across all conditions. Peak values are identified as the greatest local maxima during the first half of stance. We will use linear mixed-effects models to identify statistically significant differences in gait temporal-spatial and biomechanical variables. The fixed effects for our study will be the average differences in gait biomechanical and temporal-spatial variables by prosthetic foot type. For example, we will use a linear mixed effects regression to examine the relationship between intact knee peak EAM and prosthetic foot condition. Peak intact knee EAM will be the dependent variable, while foot condition will be the independent variable and subject by foot condition will be modeled as random effects. In the case of significance, pair-wise comparisons will be tested for significance using linear contrasts with Tukey's Honestly

Significant Difference or applying Bonferroni's correction. We will also use linear mixed effects regression to determine the association between prosthetic peak ankle power and foot condition.

### Specific Aim 3

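### The Aim 2 hypotheses concern gait symmetry, but the stated Aim 2 analysis defines no between-limb outcome, its peak window misses push-off, and it has no speed term

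*Protocol*

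**What the plan says.** **Hypotheses (Protocol, Specific Aim 2).** Each of the five is worded as symmetry.

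- 2.1: push-off forces "will be most symmetrical to the intact limb for active plantarflexion devices".
- 2.2: "Biomechanical symmetry in gait while negotiating a decline will be greater for both active plantarflexion ESR and articulating ankle ESR conditions".
- 2.3: "Biomechanical symmetry in gait while negotiating an incline will be greatest for devices with active plantarflexion".
- 2.4: "Ambulation at a faster than self-selected walking speed will yield decreased symmetry in articulating ankle ESR and non-articulating ESR feet", but not in the active plantarflexion feet.
- 2.5: "Articulating ESR feet will not yield significant differences in gait symmetry regardless of specific foot assigned".

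**Analysis (Protocol, SA2 Statistical Analysis).** The section states that its purpose is to address these hypotheses. It lists temporal-spatial variables, peak joint angles, moments and powers, knee adduction measures and peak ground reaction forces, which "will be measured and statistically compared across all conditions". The model is a linear mixed-effects regression: "The fixed effects for our study will be the average differences in gait biomechanical and temporal-spatial variables by prosthetic foot type". Two models are spelled out, one for the peak adduction moment of the intact knee and one for peak ankle power of the prosthesis. Peaks are defined as the largest local maxima in the first half of stance.

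**Data.** Level-ground walking yields kinetic and kinematic data at three controlled speeds (Gait Analysis, Procedure). On ramps there is "additional kinematic evaluation on inclines and declines" only (Specific Aim 2). SA2 Data Analysis computes joint powers for both limbs over stance, but specifies frontal-plane knee moments for the unaffected leg only.

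**Power (Power Analysis, Specific Aim 2).** 30 subjects, within-group SD 10, a 6-unit difference, alpha 5%, power 72%, for unnamed kinematic and kinetic measures.

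**The concern.** Symmetry is a relation between two limbs. An analysis that asks whether a gait variable differs between feet, one limb at a time, answers a different question, because the intact limb may also change with the foot. An analyst who follows the section as written obtains foot effects but no estimate or test of symmetry for any of the five hypotheses.

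If the symmetry measure is chosen only later, the choice of variable, scale and gait phase can be made with data in view. The protocol plans interim analyses by the site investigators at 25%, 50% and 75% enrolment (Data Management), so that is a practical possibility.

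**Working it through.** **1. Hypotheses against the stated analysis**

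| Hypothesis | Needs | Stated analysis supplies |
|---|---|---|
| 2.1 | Between-limb comparison of force at push-off/terminal stance | Peak force by foot, with peaks from the first half of stance |
| 2.2, 2.3 | Between-limb comparison on decline and incline | Variables by foot; kinematic data only on ramps |
| 2.4 | Change of asymmetry with speed, by foot | Variables by foot; no speed term stated |
| 2.5 | Asymmetry compared between articulating feet | Variables by foot; no asymmetry variable |

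Specific Aim 2, Gait Analysis, SA2 Data Analysis, SA2 Statistical Analysis and the Aim 2 power text contain no between-limb difference, ratio, index, limb term or limb-by-foot interaction.

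**2. Why a one-limb effect does not identify symmetry**

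Let P and I be the prosthetic and intact values under a given foot, and G = |P − I| the gap. A model for the prosthetic limb estimates the change in P. That says nothing about G unless the change in I is also brought in. With assumed values:

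- Equal shift: P 90 to 95, I 110 to 115. Change in P = +5. G = 20 before and 115 − 95 = 20 after, so symmetry is unchanged.
- Larger intact shift: P 90 to 95, I 110 to 120. Change in P = +5. G goes from 110 − 90 = 20 to 120 − 95 = 25, which is 25/20 = 1.25, or 25% worse.
- The second case as a normalised index, G / [0.5 × (P + I)]: 20/100 = 0.200 before and 25/107.5 = 0.233 after, about 16% worse. The direction is the same on both scales.

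Modelling the intact limb separately would show its +10, but the section states no test that sets +10 against +5.

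**3. Peak window**

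Hypothesis 2.1 concerns push-off/terminal stance, which lies late in stance. A peak confined to the first half of stance leaves that event out, so the defined force peak is not the hypothesised quantity on either limb.

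**4. Power**

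*The stated 72%.* Inputs are n = 30, SD 10, difference 6, alpha 5%. The within-subject correlation ρ between feet is not given. For a three-condition repeated-measures F test, λ = n Σ(μ − μ̄)² / [SD² (1 − ρ)], with 2 and 58 degrees of freedom.

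- Third mean midway: Σ = 9 + 0 + 9 = 18, so λ = 5.4 at ρ = 0. Power is 51.4% at ρ = 0, 67.7% at 0.3 and 74.8% at 0.4.
- Two means equal: Σ = 4 + 4 + 16 = 24, so λ = 7.2 at ρ = 0. Power is 64.4% at ρ = 0, 80.6% at 0.3 and 86.5% at 0.4.
- Two-sided paired t-test: 61.3% at ρ = 0, 70.9% at 0.2, 76.6% at 0.3.

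So 72% needs an unstated ρ of about 0.15 to 0.36, depending on the test and mean pattern, or a one-sided paired test (73.4% at ρ = 0). It can be neither confirmed nor refuted from the stated inputs.

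*On a symmetry scale.* Assume each limb has SD 10, the between-limb correlation is r, and the outcome is the signed difference. Its SD is 10 √[2(1 − r)]. For a 6-unit change in that difference, n = 30, two-sided 5%, both mean patterns and ρ from 0 to 0.5:

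| r | SD of difference | Power |
|---|---|---|
| 0 | 14.1 | 28% to 64% |
| 0.5 | 10.0 | 51% to 92% |
| 0.9 | 4.5 | above 99% |

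The protocol gives neither r nor ρ, nor a target difference in symmetry. The range shows only that 72% does not carry over.

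**The case against.** The best defence is that this is detail for a separate statistical analysis plan, which was not available. The list of variables is open-ended and covers joints on both sides, one worked model is offered only as an example, and powers are computed for both limbs. Nothing forbids a symmetry variable. This stands so far as it goes: the protocol does not rule out testing symmetry, and does not say that every variable will be analysed only as a one-limb value. It does not remove the point, because the protocol names the variables and the model, says they address these hypotheses, and what it names does not do so. The peak window is a positive statement that conflicts with Hypothesis 2.1, not an omission.

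A reader might infer more than the documents support:

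- *That all five hypotheses name the intact limb.* Only 2.1 does. For the others, between-limb symmetry is the natural reading in unilateral amputees, but it is a reading.
- *That Hypotheses 2.2 and 2.3 cannot be tested because ramps yield no kinetics.* Kinematic and temporal variables are biomechanical and can carry a symmetry comparison. The protocol never promises ramp kinetics.
- *That the Aim 3 prediction model is invalidated.* It predicts patient preference, and one-limb variables are legitimate predictors there.
- *That a misleading conclusion is likely.* The numerical example is invented and shows only that one is possible. The same plan could also report the intact-limb change.

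**Conclusion.** The concern holds as a mismatch between hypotheses and analysis. None of Hypotheses 2.1 to 2.5 has a stated dependent variable or model term that measures symmetry. Hypothesis 2.1 also has its peak in the wrong part of stance, and Hypothesis 2.4 has no stated speed term. The conclusion rests on the protocol text and on reading gait symmetry as prosthetic against intact limb. It does not depend on any power figure.

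The size of the resulting error cannot be given, since the documents contain no between-limb data. The weakness is confined to Aim 2, a subset of 30 subjects, and can be repaired from measurements already planned. The 72% power is not shown to be wrong. It simply is not a statement about symmetry.

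**What to change.** Amend SA2 Statistical Analysis, preferably before the first interim analysis at 25% enrolment:

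- **Outcome.** For each Aim 2 hypothesis, make the dependent variable a between-limb asymmetry per subject, foot and speed or ramp condition. Use the absolute prosthetic-minus-intact difference, so that cases with the prosthetic limb larger and cases with the intact limb larger do not cancel. Use a normalised index only for strictly positive variables such as ground reaction force, step length and stance time. It is unstable for joint angles, which can be near zero or of opposite sign.
- **Alternative model.** Enter both limbs in the mixed model with limb side and a limb-by-foot interaction. This tests the signed gap, so it answers the same question where the gap keeps one direction.
- **Hypothesis 2.1.** Take the ground reaction force peak in terminal stance.
- **Hypotheses 2.2 and 2.3.** Name the kinematic and temporal variables to be used on ramps.
- **Hypothesis 2.4.** Test a foot-by-speed interaction on asymmetry, and say which controlled speed stands for the faster one.
- **One-limb variables.** Keep them as secondary description.
- **Power.** Restate the 72% with an SD and target difference on the symmetry scale, or mark it as not applying to symmetry.

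The cost is modest. No new visits or trials are needed. Some processing is added: terminal-stance peaks, between-limb variables and, if symmetry of the knee adduction moment is wanted, that moment on the prosthetic side. The restated power may prove lower than 72%.

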**Procedure:** During each experimental session, subjects will walk at 3 speeds across a 10 meter instrumented walkway until 5 trials when each foot makes full contact with each force plate for at least two sequential foot strikes. Since kinetic outcome measures are speed dependent, subjects will ambulate with controlled speeds determined by normalizing to each subject's intact limb length (41). Subjects will walk at their defined median Froude speed (FR3) and at one speed below and one speed above the median (FR2 & FR4), respectively. Auditory feedback will be provided to the subject in the form of a tone to ensure that they are walking at the correct speed. Subjects will be asked to repeat the walking trials until 5 acceptable trials for each speed are collected. The main purpose of this session is to collect joint motion data, force, torque, and power on subjects during each test condition. Segment ranges of motion, velocities and accelerations, and corresponding hip, knee, and ankle joint moments of force and generated/absorbed powers will be computed using inverse dynamics methods. Averages, maximum and minimum values, standard deviations and coefficients of variation will be computed for the values attained per gait cycle over each trial and for each set of trials. Spatial and temporal parameters, such as stride and step lengths, step times and velocities will also be recorded.

Additionally subjects in this subset will perform ramp ascent and descent under the collection of kinematic data. This will be performed on a standardize ramp of 1:6 rise:run ratio, which is steeper than ADA guidelines. Subjects will be instructed to ambulate at a comfortable self-selected walking speed. This will include 5 trials ascending and 5 trials descending.

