#### Power Analysis:

| Site                                                | n   | n for subset |
|-----------------------------------------------------|------------|---------------------|
| VA New York Harbor Healthcare System (NYC)          | 30         | 15                  |
| Walter Reed National Military Medical Center (D.C.) | 30         | 15                  |
| VA Puget Sound Healthcare System (Seattle)          | 30         | 0                   |
| James J. Peters VA Medical Center (Tampa)           | 30         | 0                   |
| TOTAL                                        | 120 | 30           |

Figure 7. Total Subjects per site to be seen over the course of 3 year period

#### Specific Aim 1

Functional measures will be analyzed by multilevel (site) repeated measures analysis of variance. Because order of prosthesis will be randomized, there should be no order effect. However, order will be included in the initial analysis to test this assumption. Assuming an alpha error rate of 5% and within-group standard deviation of 5, 120 subjects will provide over 98% power to detect a 3 unit difference between at least two of the ESR groups for each of the functional measures.

### Specific Aim 2

Kinematic and kinetic measures will be analyzed by multilevel (site) repeated measures analysis of variance. Because order of prosthesis will be randomized, there should be no order effect. However, order will be included in the initial analysis to test this assumption. Assuming an alpha error rate of 5% and within-group standard deviation of 10, 30 subjects will provide 72% power to detect a 6-unit difference between at least two of the ESR groups for each of the measures.

### Specific Aim 3

This analysis will be performed using paired t-test to determine correlations between prosthesis chosen as per SAM data and which functional outcome measures are indicative of that choice. Additionally pair t-test will be performed between kinematic and kinetic data to again correlate with the prosthetic choice of the subject as demonstrated through the SAM data. Finally all SAM data will be evaluated against the activity journal to determine the roll of a specific activity goal and a specific prosthesis.

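### The Aim 2 mixed model names only subject-by-foot as random, which on its literal reading drops the within-subject comparison and does not match the repeated-measures analysis behind the stated 72% power.

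*Protocol*

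**What the plan says.** Each Aim 2 participant is measured on all three feet. The Specific Aim 2 section describes 30 "subjects which will undergo kinematic and kinetic biomechanical evaluations at the completion of each acclimation period for Parts 2-4". The Gait Analysis procedure yields replicates within each foot: "Subjects will be asked to repeat the walking trials until 5 acceptable trials for each speed are collected".

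SA2 Statistical Analysis chooses linear mixed-effects models for all gait variables and illustrates them with one outcome: "For example, we will use a linear mixed effects regression to examine the relationship between intact knee peak EAM and prosthetic foot condition". It then gives the structure: "foot condition will be the independent variable and subject by foot condition will be modeled as random effects". No other random-effects statement is made for Aim 2, and neither site nor order is mentioned there.

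The Power Analysis, under Specific Aim 2, says of the same outcomes: "Kinematic and kinetic measures will be analyzed by multilevel (site) repeated measures analysis of variance". It adds that order will enter the initial analysis. It sets alpha at 5% and takes 10 as the SD within each group. Its power claim is that "30 subjects will provide 72% power to detect a 6-unit difference between at least two of the ESR groups for each of the measures".

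**The concern.** Aim 2 compares feet within the same person. The efficiency of that design comes from removing stable differences between people from the error of each foot contrast, and a mixed model does this only if its random part links a subject's three conditions. A random intercept for each subject-foot cell, with no subject term, does not: two cells from one subject are modelled as independently as two cells from different subjects. The analysis then behaves like a comparison of 90 people in three parallel groups.

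If an analyst fitted that model, between-subject variance would stay in the error term, the test would be conservative, and a null result on the Aim 2 hypotheses could come from the model rather than from the feet. The example is the only template in the protocol, so it could be carried over to every gait variable.

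Separately, and however the phrase is read, the two sections name different analyses for the same measures, and only one of them carries the power figure.

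**Working it through.** **Inputs.** From the Power Analysis: n = 30, SD = 10, largest difference 6, alpha 5%. From Specific Aim 2: three conditions per subject. Assumed: the within-subject correlation r, which the protocol does not give, and the pattern of the three means. Two patterns with a 6-unit range are used: (-3, 0, 3), with sum of squared deviations 18, and (0, 0, 6), with 24.

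**The plan's 72%.** It cannot be reproduced without r.
- Three independent groups of 30, F test on (2, 87) df: 52% for (-3, 0, 3), 65% for (0, 0, 6).
- Two-sample comparison of 30 per group: 63 to 64% two-sided, 75% one-sided.
- Paired t-test with SD of differences 10: 89%.
- Repeated-measures ANOVA: 72% at r about 0.36 for (-3, 0, 3), or r about 0.15 for (0, 0, 6).

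So 72% lies above both independent-groups F-test values and fits a repeated-measures analysis with a modest correlation.

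**Model with a subject effect.** On balanced cell means this is repeated-measures ANOVA: noncentral F on (2, 58) df with lambda = n × (sum of squared deviations) / [SD² × (1 − r)].
- (-3, 0, 3), r = 0.34: 30 × 18 / (100 × 0.66) = 8.18, power 70%.
- (-3, 0, 3), r = 0.5: 540 / 50 = 10.8, power 82.5%.
- (-3, 0, 3), r = 0.7: 540 / 30 = 18, power 97%.
- (0, 0, 6), r = 0.15: 720 / 85 = 8.47, power 72%.
- (0, 0, 6), r = 0.5: 720 / 50 = 14.4, power 92%.

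**Literal model (subject-by-foot intercept only).** On cell means this is a one-way ANOVA with 3 × 30 − 3 = 87 error df. Its error mean square estimates the full 100 instead of 100 × (1 − r). Because the data remain correlated, its power and type I error were simulated (at least 20,000 trials per setting).

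| r | Means | Literal model | With subject effect | Type I error, literal |
|---|---|---|---|---|
| 0 | -3, 0, 3 | 52% | 51% | 5% |
| 0 | 0, 0, 6 | 65% | 64% | 5% |
| 0.15 | 0, 0, 6 | 65% | 72% | about 3% |
| 0.34 | -3, 0, 3 | 49% | 70% | 1.2% |
| 0.5 | -3, 0, 3 | 47% | 82.5% | 0.4% |
| 0.5 | 0, 0, 6 | 66% | 92% | 0.4% |
| 0.7 | -3, 0, 3 | 44% | 97% | 0.02% |
| 0.7 | 0, 0, 6 | 67% | 99% | 0.02% |

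**Does the reading matter?** The standard error of a foot contrast at r = 0.7 answers this. The literal model reports about √(2 × 100 / 30) = 2.58; with a subject effect it is √(2 × 100 × 0.3 / 30) = 1.41. A small trial-level fit (30 simulated datasets, 5 trials per cell, some convergence warnings) gave mean standard errors of 2.51 for subject-by-foot only, 1.43 for subject plus subject-by-foot, and 1.46 for foot effects random within subject. The last reading keeps the crossover's precision.

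**The case against.** The phrase is informal prose, not a model formula, and it uses the plural for the random effects. It can fairly mean foot effects that vary within subject, which links the three feet and costs almost nothing in precision. The sentence is offered as an example for one variable, and the Power Analysis shows that the repeated-measures design was recognised. All of this stands. A reader might infer that the plan as written definitely treats a subject's feet as unrelated and has lost the crossover's power; the text is too ambiguous to support that.

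Nor does averaging the five trials settle the reading. With one average per subject-foot cell, the cell effect cannot be separated from the residual under either reading. The Gait Analysis procedure also summarises both single trials and sets of trials, and nothing says that the model is fitted to averages.

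The size of the loss rests on a correlation that the protocol does not give. Quoting only the larger losses would mislead: the gap is about 7 points at r = 0.15 with means 0, 0, 6, and nil at r = 0.

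A last objection is that the random structure belongs in the statistical analysis plan. That would answer a protocol that was silent. This one states a structure, and states beside it a power figure for a differently named analysis.

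**Conclusion.** The point holds as an ambiguity with a harmful literal reading, together with an unreconciled difference between two sections. It does not hold as a demonstrated loss of power.

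If the literal model is fitted, the loss with means -3, 0, 3 is about 21 points at r = 0.34 (70 − 49), 35 points at r = 0.5 (82.5 − 47) and 53 points at r = 0.7 (97 − 44). With means 0, 0, 6 it is 7 points at r = 0.15 and 26 points at r = 0.5 (92 − 66). At the correlations that reproduce the plan's own 72%, the literal model gives about 49% (r = 0.36, means -3, 0, 3) or 65% (r = 0.15, means 0, 0, 6), so it falls short of that figure under both patterns. The type I error stays below 5%: the risk is of missed differences, not of false ones.

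These figures assume equal variances, one common correlation between feet, complete data from 30 subjects, and the plan's SD and difference. The mismatch between the two sections needs none of these assumptions.

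**What to change.** In SA2 Statistical Analysis, replace the random-effects clause with a random intercept for subject, plus a random subject-by-foot intercept only when individual trials are modelled. When the five trials are averaged to one value per subject and foot, keep the subject intercept alone. Say which of the two data forms will be analysed.

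Name this same model in SA2 Statistical Analysis and in the Specific Aim 2 part of the Power Analysis, and carry into the former the site and order terms that the latter already states.

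The cost is wording in two sections and one more variance component to estimate. No new data or participants are needed.
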